### Baseline, post-intervention, and follow-up assessments

Questionnaire data will be gathered at three time points: baseline, post-intervention, and 3-month follow-up. Because the study will be implemented in two waves, there will be a total of six assessments, three in each wave. This is depicted in the SPIRIT figure chart in Fig. 2.

**Fig. 2 Fig2:**
[figure not shown]
Standard Protocol Items Recommendations for Interventional Trials (SPIRIT): Schedule of enrolment, interventions, and assessments for trial of CSI

Participant flow, from enrollment through the 3-month follow-up assessment, can be seen in Fig. 3.

**Fig. 3 Fig3:**
[figure not shown]
Study flow chart

### Retention of participants in the study following post-intervention assessment

In the pilot study, retention of the WLC group was facilitated by periodic WhatsApp text messages reminding WLC participants of the post-intervention assessment and the CSI intervention that would follow shortly thereafter. In the present study, there will be an additional three and a half month period due to the follow-up assessment before the WLC group receives the intervention. In order to maintain interest in the study, a separate social event will be held for the WLC and CSI groups in each wave. The event will be a gathering in a park or community center with food and music for a few hours, and will occur during the month following the post-intervention assessment.

### Statistical power and sample size

A target of 480 caregivers (240 families) will be recruited in two waves. We initially calculated a sample size based on 90% power at 5% level of significance and an attrition rate of 20%, yielding a sample of 432 individuals or 216 families. However, because we aim to have 12 participants in each CSI group, we increased the sample size to 480 (240 families). Dividing the sample over two waves, with randomization into CSI and waitlist control in each wave, this sample size yields a total of ten CSI groups per wave (five for women and five for men), for a total of 20 CSI groups.

Target population and parameters: The primary target population is Syrian refugees living in northern Lebanon, with secondary populations being Palestinian refugee and Lebanese families in the same or adjacent communities, who have at least one child 3–12 years old. In our pilot study of the CSI, the baseline total score of our newly developed parenting scale was 61.6. This is a new scale so there are no direct comparisons from the literature about the expected mean total score of this measure. The mean total score of parenting following the CSI intervention was 63.7 at 9 weeks. As our primary outcome is a continuous variable, it can be described by the normal distribution. The final analysis will incorporate baseline mean rate as a covariate to improve the precision of the estimate of the treatment difference between groups. In order to estimate the within-group correlation between baseline and outcome rate (of total parenting score) we ran a Pearson’s correlation between baseline and 9-week scores in the CSI pilot study, giving a point estimate of ρ = 0.6. The intra-class correlation has been estimated at 0.15 based on a random intercept regression model with total parenting score as the outcome, CSI group as the intervention, and adjusting for baseline total parenting score. The STATA command *clustersampsi* was used for the power and sample calculation.

#### Data analysis

The statistical analyses will be carried out by the trial statistician, who will remain blind to the group randomization until the main analyses are complete. The analyses outlined in this strategy will be primarily based on an intention to treat (ITT); a per protocol (PP) analysis will be the secondary analysis. The PP analysis will include participants who complete the CSI, with completion defined as attending at least seven of the nine sessions, and will exclude any participant who attended fewer than seven sessions. We have powered the study (see the “Sample size” section) as a superiority study at 10 weeks. The first stage of analyses will be a descriptive model of the data to assess completeness of data and the integrity of the data collection system. Participants and area characteristics and demographics will be summarized at baseline. Clinical characteristics that have been measured repeatedly will be summarized at baseline and at the post-randomization follow-up assessments. In addition, patterns of missing data will be described.

The primary outcome (total score of parenting scale) will be analyzed using linear mixed models to model the mean difference in the total score of parenting scale 10 weeks post-randomization. The linear mixed models will be adjusted for baseline total score of parenting scale and stratification. A two-level hierarchical model will be employed to improve power and take into account clustering of the parents at the family level.

These models utilize maximum likelihood estimation and thus allow for missing outcome data under the missing at random (MAR) assumption. Associations between post-randomization variables and missingness will be dealt with by multiple imputation (MI), again under the MAR assumption. Departures from this assumption will be assessed with a sensitivity analysis.

Secondary outcomes, including parental warmth and responsiveness, harsh parenting, parenting knowledge, caregiver psychosocial wellbeing, and child psychosocial wellbeing will be assessed with a similar methodology used for the primary outcomes, using generalized linear mixed models depending on the type of outcome (normal, ordinal).

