### Control group

This study is employing a waitlist control as the comparison group, based on our successful use of the same design in the pilot RCT of the CSI. Participants in the waitlist control group in each wave of the study will be invited to participate in CSI groups that will begin shortly after the 3-month follow-up assessment has been completed.

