## Discussion

The CSI was developed with the aim of strengthening parenting in refugee communities by [1] lowering the stress and increasing the psychosocial wellbeing of refugee parents, and [2] strengthening their parenting knowledge and skills. The ultimate aim is to create an evidence-based, scalable intervention that can be adapted and implemented in diverse refugee communities and contexts. The emphasis in the CSI on strengthening parental wellbeing as an approach to improving parenting represents a shift from conventional parent training programs, which prioritize the acquisition of knowledge and skills. If the findings of this study support the model underlying the CSI, this will lend support to the idea that parenting in settings of adversity can be strengthened by addressing parents’ own wellbeing as well as by increasing and their knowledge and skills.

A second contribution of this study, if our methods are effective, will be to demonstrate the feasibility of recruiting and retaining men/male caregivers in a parenting intervention. Panter-Brick et al*.* [30] have cautioned that the paucity of men in parenting interventions may be undermining the effectiveness of such programs, both because men may not support the changes their partners are trying to make at home and because men may continue to engage in problematic parenting behaviors themselves. In our pilot RCT of the CSI ([name], [name], [name], [name], [name], [name], et al.: Supporting families displaced by armed conflict: A pilot randomized controlled trial of the caregiver support intervention, submitted), we successfully recruited both caregivers in our target of 72 families, of whom 86% completed at least seven of the nine sessions. If we are able to successfully recruit 240 families in which both caregivers participate, we believe this may challenge the widespread perception that men are uninterested and unwilling to participate in parent-focused interventions.

Finally, we acknowledge the trade-off in deciding to focus exclusively on families in which both caregivers are willing to participate in the study. If this trial establishes the effectiveness of the CSI in families with both caregivers participating, it will be unclear to what extent we can expect to achieve similar effects in families with only one participating caregiver.

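### The per-protocol rule leaves no control group if read literally, and a non-randomized comparison if applied to the CSI arm only

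*Protocol article*

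**What the plan says.** The Data analysis section bases the main analysis on ITT and adds that "a per protocol (PP) analysis will be the secondary analysis". It fixes the PP set in two matching statements. The inclusion side reads "The PP analysis will include participants who complete the CSI, with completion defined as attending at least seven of the nine sessions". The exclusion side says that the analysis "will exclude any participant who attended fewer than seven sessions". Neither is limited to the CSI arm, and nothing says how waitlist caregivers enter the PP set.

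The Control group section says that waitlist participants "will be invited to participate in CSI groups that will begin shortly after the 3-month follow-up assessment has been completed". The primary contrast, in Data analysis, is the "mean difference in the total score of parenting scale 10 weeks post-randomization". Both outcome assessments therefore come before any control has been offered a session.

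The Discussion reports pilot attendance for the target of 72 families, "of whom 86% completed at least seven of the nine sessions".

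**The concern.** A PP analysis is a comparison between arms, so both arms need a route into it. Here membership depends on an exposure that only one arm can have. Applied as written, the rule leaves nothing to compare.

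The natural repair is to apply the threshold to the CSI arm only. That gives a contrast, but it selects on behaviour after randomization in one arm and leaves the other unselected. The waitlist arm also contains caregivers who would have attended fewer than seven sessions, and they stay in.

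The protocol gives reasons to think that low attenders may differ. Recruitment treats income-generating work as a barrier for men. The discontinuation criteria let a repeatedly disruptive participant be asked to leave the intervention while staying in the study. The Background links caregiver stress to parenting, the outcome domain.

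At stake is the only planned estimate of the effect of completing the CSI. A difference in PP could reflect who attends as well as what the CSI does.

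**Working it through.** The plan attaches no figure to the PP analysis, so there is none to reproduce. The check is a count, followed by a bias calculation.

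**Inputs from the protocol**
- Caregivers per arm: 240, from 120 families (Randomization and blinding).
- PP threshold: at least 7 of 9 sessions (Data analysis).
- Sessions offered to controls before the 3-month follow-up: 0 (Control group).
- Pilot completion: 86% (Discussion). The sentence can be read as counting families or caregivers.
- Baseline-to-outcome correlation: 0.6 (Statistical power and sample size).

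**Step 1, literal reading.** Every control has 0 sessions, and 0 < 7. Excluded: 240 of 240. Controls left: 0.

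**Step 2, CSI-only reading.** CSI caregivers kept: 0.86 × 240 = 206.4, about 206. Excluded: about 34, or 14%. Controls kept: 240. At 70% to 80% completion the CSI count would be 168 to 192. Attrition is ignored throughout.

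**Step 3, bias of the CSI-only contrast.** Let c be the share who would complete if offered the CSI. Let A and N be the mean untreated outcomes of would-be completers and non-completers, after baseline adjustment. The right comparator for completers has mean A. The controls supply c·A + (1 − c)·N. Hence

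bias = A − [c·A + (1 − c)·N] = (1 − c) × (A − N).

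**Step 4, numbers.** The gap A − N is not in the protocol. These values are assumptions:

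| Excluded share | Gap 0.2 SD | Gap 0.5 SD |
|---|---|---|
| 14% (pilot) | 0.14 × 0.2 = 0.028 | 0.14 × 0.5 = 0.070 |
| 20% (assumed) | 0.20 × 0.2 = 0.040 | 0.20 × 0.5 = 0.100 |
| 30% (assumed) | 0.30 × 0.2 = 0.060 | 0.30 × 0.5 = 0.150 |

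The gap must be the one left after adjustment, because the planned model includes the baseline score. For example, if attenders and non-attenders differ by 0.5 SD at baseline and by 0.5 SD at outcome, with equal SDs and correlation 0.6, the adjusted gap is 0.5 − 0.6 × 0.5 = 0.2 SD. That is the first column.

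**Step 5, cross-check with another model.** Suppose attendance follows a normal latent propensity that correlates r with the adjusted outcome. Then bias = r × φ(t)/c, with t = z(1 − c). At c = 0.86, φ(t)/c is about 0.26. For assumed r of 0.1 to 0.4, the bias is 0.03 to 0.10 SD of the adjusted outcome. With no true effect and a design effect of 1.15 (families of two, intra-class correlation 0.15), a nominal 5% test would reject 5.7% to 17.4% of the time.

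**The case against.** **The literal reading is a slip.** A PP analysis with no comparator cannot have been intended, and completion is naturally read as applying to those offered the CSI. This is fair, and a few words would correct it. But correcting it leaves the selected contrast of Step 2. Nor is this a detail left to an unseen SAP: the article states the rule.

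**Any PP set has this weakness, and ITT is primary.** Also fair. Nothing in the protocol lets PP replace ITT. This limits how much the point matters, but it does not make the contrast randomized.

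Stronger readings that the documents do not support:
- *The bias favours the CSI.* The protocol reports no relation between attendance and outcome. Work conflicts do not imply poorer parenting, and caregivers in greater need might attend more. The direction is unknown.
- *The bias is a large share of the target effect.* The protocol states neither an SD nor a target difference. Back-solving from 432 participants and the pilot change of 63.7 − 61.6 = 2.1 gives about 0.29 to 0.57 SD, depending on cluster size and use of the baseline correlation. No percentage of target is reliable.
- *Excluding one caregiver of a pair breaks the model.* A family random intercept accommodates one-member families.
- *A complier analysis is free of bias.* Minimization of contamination asks CSI participants not to share content outside the immediate household, so sharing between partners is not barred. A non-attender whose partner attends may benefit, which threatens the exclusion restriction at caregiver level.

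**Conclusion.** The point stands and should be corrected, although it concerns a secondary analysis. As worded, the PP rule removes all 240 controls. Under the likely intended reading, it compares about 206 attenders selected after randomization with 240 unselected controls.

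At the pilot completion rate the bias would be modest: about 0.03 to 0.07 SD for assumed adjusted gaps of 0.2 to 0.5 SD, with its sign unknown. It grows in proportion to the excluded share. These figures rest on the assumed gaps and on a pilot rate whose unit is unclear. The count in Step 1 rests on no assumption. A reader should not infer that the trial's main conclusion is at risk, because ITT keeps every randomized caregiver.

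**What to change.** 1. **Repair the PP definition.** Apply the seven-session rule to the CSI arm only and keep all waitlist caregivers. Adjust for baseline predictors of attendance. Label the result as a supportive, non-randomized comparison.

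2. **Make a complier-average causal effect the main estimate of the effect of receiving the CSI.** Keep all randomized caregivers. Use randomized arm as the instrument for attending at least seven sessions, with baseline score and randomization strata as covariates and family-clustered errors. With no uptake among controls, the simple ratio form is ITT ÷ 0.86 = 1.16 × ITT at the pilot rate.

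3. **State the exclusion restriction and test it.** It says that allocation has no effect on caregivers below seven sessions, so partial attendance and content shared at home are assumed to do nothing. Add a sensitivity analysis with uptake defined by family, for example at least one caregiver attending seven or more sessions.

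Only CSI caregivers have attendance during the trial period, so either analysis reveals allocation and should follow the blinded main analysis.

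The cost is analysis wording. Attendance registers are already planned for all CSI groups (Intervention fidelity assessment, quality control, and supervision). The downsides are an interval wider than that of ITT, by about the same factor of 1.16 in the simple ratio form, and reliance on the stated assumption.

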## Background

Studies and field reports indicate that chronic adversity is generating high levels of stress among Syrian caregivers (in this paper, we use the term *caregivers* to refer to any primary caregivers of children, most but not all of whom are their biological parents). This includes those still in Syria as well as Syrian refugees in Lebanon and other adjacent countries [1–5]. In addition to coping with the impact of war-related experiences of violence and loss, Syrian refugee caregivers are contending with a host of ongoing stressors. These include poverty, inadequate and unsafe housing, severe restrictions on employment, a lack of access to healthcare, limited educational opportunities for their children, and the loss of social support networks [6–9].

Persistently high stress depletes caregivers’ coping resources and has been linked to compromised parenting, including unresponsive, overprotective, and harsh parenting. Compromised parenting, in turn, poses significant risks to children’s psychosocial and cognitive development [10–13]. For young children, it also represents a threat to the development of healthy attachments. Highly stressed and anxious caregivers are significantly more likely to have children with insecure attachments, which pose a risk for subsequent difficulties in children’s self-regulation, interpersonal relationships, and future academic achievement [12–15]. The linkages among parental stress, compromised parenting, and child mental health and psychosocial difficulties have been well-documented in studies of diverse refugee communities [6, 7, 16–19], including Syrian refugees in Lebanon [7, 20], the target population in the present study.

In response to growing evidence demonstrating the mediating role of parenting in shaping children’s responses to armed conflict and forced migration, non-governmental organizations (NGOs) have developed or adapted interventions aimed at strengthening parenting in refugee families. The primary emphasis in most such programs is on strengthening parenting knowledge and skills. This emphasis assumes, at least implicitly, that a deficit in parenting knowledge and skills underlies suboptimal parenting in highly stressed refugee families. An alternative hypothesis, supported by a growing number of studies, is that compromised parenting in refugee families reflects, at least partly, the impact of chronic adversity on the ability to parent effectively [6, 7, 18].

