## Methods/design

### Design

This will be a parallel group superiority RCT with an intent to treat design, a 1:1 allocation ratio, and a waitlist control comparison group. The study will be conducted in two waves, due to the large number of participants. Recruitment for each wave will take place in the neighborhoods of greater Tripoli (see the “Setting” section), with wave 2 recruitment starting during implementation of wave 1. This will help us ensure a high quality of implementation and rigorous data collection at all assessment points.

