**Fig. 4 Fig4:**
[figure not shown]
Putative mediation of impact of CSI on parenting by caregiver stress, caregiver distress, caregiver psychosocial wellbeing, and stress management. Solid lines represent mediational pathways to be tested

Since all the measures are continuous, the indirect effects will be calculated by multiplying relevant pathways and bootstrapping will be used to produce valid standard errors for the indirect effects. All analyses will adjust for baseline measures of the mediators (Caregiver Stress Scale, caregiver distress (K10), stress management, outcome (Parenting scale) and putative measured confounders (e.g., socioeconomic status).

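### Baseline caregiver stress and K10 could be added to the primary model and the imputation model at almost no cost; the model as stated is valid, and the expected gain is modest

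*Protocol article*

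**What the plan says.** Data analysis gives the covariates of the primary linear mixed model: "The linear mixed models will be adjusted for baseline total score of parenting scale and stratification". No other covariate is named. The section relies on maximum likelihood under missing at random (MAR) and then adds: "Associations between post-randomization variables and missingness will be dealt with by multiple imputation (MI), again under the MAR assumption". It also promises a description of missing-data patterns and a sensitivity analysis for departures from MAR.

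Statistical power and sample size gives precision as the reason for adjusting for baseline parenting, with a baseline-to-outcome correlation of 0.6.

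The Caregiver Stress Scale and the K10 are in the questionnaire battery (Measures, Table 2). The battery is given at baseline, and randomization follows it (Randomization and blinding). The Background says that persistently high stress "has been linked to compromised parenting, including unresponsive, overprotective, and harsh parenting". In the mediation section, by contrast, "All analyses will adjust for baseline measures of the mediators".

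**The concern.** A likelihood analysis under MAR is protected only with respect to the variables in the model. Suppose a baseline variable predicts both dropout and later parenting, beyond what baseline parenting explains. The primary model as stated does not condition on it, and the imputation sentence speaks only of variables measured after randomization. Baseline stress and distress are the natural candidates, because the trial's rationale rests on their effect on parenting.

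Two things are at stake. One is some precision. The other is protection against a shift in the treatment difference if more distressed caregivers are lost to a different extent in the two arms. If they leave the CSI arm more, the shift favours the CSI.

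**Working it through.** **Inputs from the protocol.** 90% power, 5% significance (two-sided assumed), 20% attrition, "a 1:1 allocation ratio", correlation 0.6, intra-class correlation 0.15, 432 participants calculated and 480 planned. The pilot means are 61.6 at baseline and 63.7 after the CSI, a difference of 2.1. Neither an SD nor an explicit target difference is given.

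**The plan's own figure.** Without an SD, 432 cannot be reproduced independently; it can only be solved backwards. Assume families of two, so the design effect is 1 + 0.15 = 1.15, and a residual variance of 1 − 0.6² = 0.64. Analysed per arm: 432 × 0.8 / 2 = 172.8. Then

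d² = 2 × (1.960 + 1.282)² × 1.15 × 0.64 / 172.8 = 0.0895, so d = 0.299 SD.

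If 2.1 points is the target, the SD is 2.1 / 0.299 = 7.0. With clusters of 12 instead, d would be about 0.45. The value 0.30 is therefore a benchmark under an assumption and not a protocol figure.

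**Standard error at the planned size.** 480 × 0.8 = 384 analysed, 192 per arm: SE = √(2 × 1.15 × 0.64 / 192) = 0.088 SD, about 0.09.

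**Precision.** Baseline parenting already removes 0.6² = 36% of outcome variance. Let p be the partial correlation of baseline stress/distress with the outcome given baseline parenting (assumed). The SE is multiplied by √(1 − p²), and the saving is 432 × p².

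| p | Change in SE | Worth, of 432 | Power at 384 analysed |
|---|---|---|---|
| 0 | none | 0 | 92.7% |
| 0.1 | −0.5% | 4 | 93.0% |
| 0.2 | −2.0% | 17 | 93.7% |
| 0.3 | −4.6% | 39 | 94.8% |

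The SE ratios do not depend on the back-solved effect; the power column does.

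**Dropout bias.** Assume a logistic dropout model in which the odds of dropout double per SD of baseline distress wherever distress matters. The bias in the treatment difference, in outcome SDs, is p × 0.8 × (difference between arms in completers' mean distress), where 0.8 = √0.64. Doubling odds with 20% loss lowers completers' mean distress by 0.129 SD; with 30% loss by 0.190 SD; with 10% loss by 0.066 SD.

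| Dropout pattern (loss CSI / waitlist) | p = 0.1 | p = 0.2 | p = 0.3 |
|---|---|---|---|
| Same slope, 20/20 | 0 | 0 | 0 |
| Slope in CSI arm only, 20/20 | 0.010 | 0.021 | 0.031 |
| Slope in CSI arm only, 30/10 | 0.015 | 0.030 | 0.046 |
| Same slope, 30/10 | 0.010 | 0.020 | 0.030 |
| Opposite slopes, 20/20 | 0.021 | 0.041 | 0.062 |

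Example: slope in CSI arm only, 20/20, p = 0.3: 0.3 × 0.8 × 0.129 = 0.031. A large-sample simulation agreed with these values to about 0.003 SD. With baseline distress in the model, the bias was about zero in every pattern.

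**The case against.** The strongest reply is that nothing here is wrong. A mixed model adjusted for the baseline outcome and stratification is a standard, valid intention-to-treat analysis, and the largest precision gain has already been taken. The imputation sentence is condensed: it says which associations prompt imputation and does not exclude baseline predictors, and an analysis plan that is not shown may list them. The partial correlations are assumed. The Background supports a link between stress and parenting, not a link of 0.2 to 0.3 once baseline parenting is held fixed. Dropout driven by distress is reported nowhere. Attrition of 20% is a planning allowance, 99% of pilot waitlist participants completed the post-intervention assessment, and retention events are planned for both arms. All of this stands, and it keeps the point optional and small.

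It does not remove the point. The covariate list is stated, not left open, and the planned sensitivity analysis has another target. Dropout explained by measured baseline distress is MAR once distress is conditioned on, so inclusion is the direct remedy.

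Three stronger readings are tempting and unsupported:

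- A reader might infer that protection against distress-related dropout has been given up. Likelihood estimation, imputation and a sensitivity analysis are all planned, and bias needs a dropout pattern or amount of loss that differs between arms.
- A reader might infer that the primary effect and the mediation effects will conflict because their covariate sets differ. Direct and indirect effects sum within the mediation model's own covariates. Under randomization without selective loss, both sets target the same total effect. Mediation also needs confounder control that a randomized comparison does not.
- A reader might extend the argument to index-child age. Nothing in the protocol or in the calculations above supports that.

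**Conclusion.** The point holds as an inexpensive improvement to a valid analysis. Two prognostic scores collected before randomization are conditioned on in neither stated step, although the trial's own model says they affect parenting.

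The likely benefit is modest: an SE lower by 0.5% to 4.6% for an assumed partial correlation of 0.1 to 0.3, in a trial with about 92.7% power under the back-solved effect. Removal of a bias of about 0.01 to 0.06 SD is a conditional benefit. It requires distress-related loss that differs between arms in pattern or amount, and even the extreme case is about 0.06 / 0.09, or two thirds of one standard error. If the pattern and the loss are the same in both arms, the gain is precision alone.

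**What to change.** Before unblinding, state that the primary parenting model adjusts for baseline parenting score, stratification, baseline Caregiver Stress Scale and baseline K10, all as fixed covariates. Use baseline values only, because later stress and distress are the putative mediators. State also that the imputation model includes the baseline scales as predictors, alongside the post-randomization variables already mentioned.

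Leave the mediation models with their own confounder set, including stress management and socioeconomic status, and do not add index-child age on this argument.

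The cost is a sentence or two of wording and two degrees of freedom, with no new data collection. The change should be made in advance, because covariates added after unblinding would look data-driven.

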### Intervention

The CSI is a nine-session weekly group intervention, co-facilitated by trained non-mental health professionals, who receive 6 days of training, three on-site observations with feedback, and weekly supervision. Groups are offered separately to women and men and are run with 10–12 participants. Table 1 lists session topics and corresponding modules, along with the stress management technique(s) taught in each session.

**Table 1 Tab1:** CSI sessions, modules, and stress management/relaxation methods

Session	Topic	Module
1	Introduction and group building *SM*: Participants’ own methods of coping with stress*	Caregiver wellbeing
2	Stress and relaxation *SM: Counting the breath*	Caregiver wellbeing
3	Lowering our stress *SM: Stepping back from our thoughts, grounding*	Caregiver wellbeing
4	Coping with frustration and anger *SM: Peaceful walking, various anger management techniques*	Caregiver wellbeing
5	Parental stress and influence *SM: Stepping back from our thoughts (repeat)*	Parenting in adversity
6	Increasing our influence as parents, part I: Positive attention *SM: Guided visualization: A safe place*	Parenting in adversity
7	Increasing our influence as parents, part 2: Effective discipline *SM: Informal breathing practice*	Parenting in adversity
8	Positive parenting: Practice *SM: Participants choose any stress management/relaxation method*	Parenting in adversity
9	Looking back, looking forward	Closure

*SM* stress management/relaxation technique taught during the session

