#### Demographics

A brief demographics form, developed for the pilot RCT, will be used to record family composition, caregiver nationality, sex, and age, ages and sex of all members of the household, years in Lebanon (if non-Lebanese), and other demographic variables relevant to the study’s outcomes.

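### Caregiver sex is recorded but left out of the primary model; adding it is a minor, nearly free safeguard in case the mix of mothers and fathers analysed differs between arms

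*Protocol article*

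**What the plan says.** In the protocol article, Data analysis, the primary outcome model is a linear mixed model "adjusted for baseline total score of parenting scale and stratification", with caregivers nested in families. Missing outcomes are handled by maximum likelihood under MAR. Multiple imputation is planned for associations between missingness and post-randomization variables, and a sensitivity analysis for departures from MAR. A secondary per-protocol analysis drops anyone who attended fewer than seven of the nine sessions.

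Sex is built into the design elsewhere:

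- Intervention: "Groups are offered separately to women and men".
- Inclusion criteria require both primary caregivers. Statistical power and sample size plans five women's and five men's CSI groups per wave. Together these imply one woman and one man per family.
- Demographics: the baseline form will "record family composition, caregiver nationality, sex, and age".
- Child psychosocial wellbeing: only female caregivers complete the KINDL, because mothers are said to spend much more time with the children.

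Randomization is by family within community (Randomization and blinding), so the stratification term cannot carry caregiver sex.

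**The concern.** The model gives both caregivers of a family the same expected score, given baseline and stratum. The protocol's own reason for restricting the KINDL to mothers suggests that mothers and fathers may differ on a parenting scale. Family-level randomization balances sex between arms only while both caregivers are analysed. There are two ways to lose that balance:

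- **Outcome loss.** The plan allows for 20% attrition. CSI families face nine weekly sessions, while waitlist families wait. If fathers are lost at different rates in the two arms, the analysed sex mix differs by arm. Likelihood-based MAR holds only given the variables in the model, and sex is not one of them.
- **Per-protocol exclusions.** The waitlist arm is offered no sessions until after the 3-month follow-up, so the seven-session rule can sensibly remove only CSI participants. If attendance differs by sex, the mix diverges even with full outcome retention.

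In either case part of the mother-father difference enters the treatment estimate.

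**Working it through.** **The plan's own figure.** Statistical power and sample size gives "90% power at 5% level of significance and an attrition rate of 20%, yielding a sample of 432 individuals or 216 families". The inputs are the pilot means ("the baseline total score of our newly developed parenting scale was 61.6" and 63.7 after the CSI, a difference of 2.1), the baseline-outcome correlation ("giving a point estimate of ρ = 0.6") and an ICC of 0.15. No SD is stated, and a two-sided test is assumed. With cluster size 2:

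n per arm = 2 × (1.960 + 1.282)² × (SD/2.1)² × (1 − 0.6²) × (1 + 0.15)

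At an assumed SD of 7 this is 171.9 caregivers, or 86 families per arm. Then 86/0.8 gives 108 families per arm, so 216 families and 432 caregivers. The figure is consistent with SD = 7 but cannot be confirmed. On that reading the design difference is 2.1/7 = 0.30 SD. Adding sex changes neither this calculation nor the planned 480.

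**Complete pairs.** Let d be the mother-father difference in residual-SD units that baseline leaves unexplained. Omitting sex raises the caregiver variance from 1 to 1 + d²/4 and lowers the within-family covariance from 0.15 to 0.15 − d²/4. The treatment contrast depends on their sum:

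1 + d²/4 + 0.15 − d²/4 = 1.15

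This is the same with or without sex. The cancellation needs a family variance estimate above zero, so d below 2√0.15 = 0.77 residual SD, or 0.77 × √(1 − 0.36) = 0.62 outcome SD. Simulation (1500 runs, 240 families) agrees: at a 0.5 SD difference the SE was 0.096 in both models when baseline carried the difference. At 0.8 SD with none carried by baseline, the family variance estimate falls to zero and the reported SE was 0.1024 against 0.0980. The actual spread hardly moved (0.0967 against 0.0966).

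**Unequal loss of fathers and mothers, same in both arms** (assumed 30% and 10%). There is no bias. With baseline carrying none of the sex difference, mean SEs without and with sex were:

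| Sex difference | Without sex | With sex | Reduction |
|---|---|---|---|
| 0.3 SD | 0.0860 | 0.0856 | 0.5% |
| 0.6 SD | 0.0879 | 0.0856 | 2.6% |

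Power for an effect of 0.35 residual SD was 89.7% in both models at 0.5 SD when baseline carried the difference. The largest gap, 88.1% against 89.9%, needed 0.8 SD with none carried.

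**Father loss that differs by arm** (assumed 20% waitlist, 35% CSI; 10% of mothers in both). Total loss is 15% and 22.5%, averaging 18.75%, which is inside the planned 20%.

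- Father share, waitlist: 0.80/(0.80 + 0.90) = 0.471
- Father share, CSI: 0.65/(0.65 + 0.90) = 0.419
- Difference in share: 0.051 (0.0512 unrounded)

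The shift is about 0.0512 × the part of the sex difference left after baseline adjustment. If baseline carries none, that part is the full difference. If baseline carries all, it is (1 − 0.6) = 0.4 of it.

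| Sex difference | Baseline carries none | Baseline carries all |
|---|---|---|
| 0.3 SD | 0.015 SD | 0.006 SD |
| 0.6 SD | 0.031 SD | 0.012 SD |

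Simulation of the same setting gave 0.016 and 0.031 to 0.032 (none), and 0.006 and 0.011 (all). At SD = 7 the range 0.006 to 0.031 SD is 0.04 to 0.22 points, or 2% to 10% of 2.1. If fathers score lower and more of them are lost from CSI, the shift favours CSI. If they score higher, it goes against it.

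**A harsher case.** With 20% against 40% father loss and sex differences of 0.2 to 0.8 SD, simulated bias without sex was 0.014 to 0.025 residual SD when baseline carried the difference, and 0.020 to 0.072 when it did not. Type I error at the extreme was 9.1% without sex and 6.0% with it. With sex in the model, bias was at most 0.006.

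**Per protocol.** The same share formula applies with attendance in place of loss. The protocol gives no attendance by sex, so I put no figure on it.

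**The case against.** The strongest reply is that leaving out one prognostic covariate is not an error. Randomization protects the comparison, and the plan already adjusts for each caregiver's own baseline score, which would carry much of any stable mother-father difference. The likelihood also conditions on arm, stratum and the partner's outcome. Imputation and an MAR sensitivity analysis are planned, and the contents of the imputation model normally belong in an analysis plan that is not shown. The pilot figures are favourable: 99% of waitlist participants completed the post-intervention assessment, and 86% is given for attendance at seven or more sessions, neither split by sex.

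Most of this stands, and it is why the point is minor. Two parts do not close it. The covariates of the primary model are stated, not left open. The imputation sentence names post-randomization variables, and sex is a baseline variable.

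A reader might also infer that men are expected to drop out more. The document does not say so. Recruitment describes special effort to enrol men, and the Discussion treats keeping them as something the trial may show to be feasible. Uncertain retention is all that can be drawn from this. Nor does higher father loss alone cause this bias; the loss must differ between arms.

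**Conclusion.** This is a minor point, a nearly free improvement and not a flaw in the design. The stated model omits a recorded variable that is balanced between arms only while both caregivers of a family are analysed.

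If father loss differs by arm by an assumed 15 percentage points and the sex difference is an assumed 0.3 to 0.6 SD, the primary estimate shifts by about 0.006 to 0.03 SD. The upper end requires that the baseline score carry none of the difference. The per-protocol estimate is open to the same shift if attendance differs by sex.

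A reader might conclude that the trial is losing precision or power. The design does not support that. The sex difference cancels in complete pairs. Over the 0.3 to 0.6 SD range any gain is at most a few percent, and it arises only when fathers and mothers are lost at different rates.

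The sex difference, the dropout by sex and the SD of 7 are assumptions. An analysis plan that is not shown may already include sex.

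**What to change.** Before unblinding, name caregiver sex as a fixed effect in the primary model, in the secondary models that use both caregivers and in the per-protocol model. Leave it out of the KINDL model, where all respondents are women. Include sex in the imputation model. The cost is one degree of freedom per model and a line of text; no new data are needed and the sample size is unchanged.

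The limit should be stated alongside. A sex main effect removes the shift due to a mother-father difference in level. It does not correct for a treatment effect that differs by sex. In simulation with 30% of fathers and 10% of mothers lost in both arms and a smaller effect in fathers, the estimate moved toward the mothers' effect by about 0.025 residual SD with or without sex in the model.
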